### Participant timeline {13}

The participant timeline includes screening, enrollment, baseline assessments, randomization, biopsy procedures, and structured follow-up over 12 months. Only men with mpMRI findings of PI-RADS 4–5 or PI-RADS 3 with PSA density > 0.15 proceed to randomization. Follow-up includes standardized complication reporting, patient-reported outcome assessments, and repeat MRI depending on biopsy results (see Fig. 1).

**Fig. 1 Fig1:**
[figure not shown]
SPIRIT schedule of enrollment, interventions and assessments for the PRIMA Trial. SPIRIT figure illustrating the structured timeline of trial procedures including screening, baseline imaging, randomization, biopsy, MR in-bore biopsy (if indicated), safety follow-up at 30 days, 12-month follow-up imaging and PROMs, and end-of-study data lock

### Sample size {14}

#### Assessment for eligibility

Men aged 50–75 with PSA elevation (≥ 3 ng/ml) and/or abnormal DRE. To be allocated to trial: *n* = 1908 (including 20% calculated loss). To be analyzed: 477 patients per randomized arm A/B (PI-RADS 4/5 and PI-RADS 3 PSAD > 0.15), resulting in *N* = 2 × 477/0.6 = 1590.

#### Sample size

The sample size is derived from the following expected PI-RADS distribution (own institutional data and PRECISION trial data [8, 23]): 25% PI-RADS 1–2, 25% PI-RADS 3 (15% PSAD ≤ 0.15 and 10% PSAD > 0.15), 30% PI-RADS 4, and 20% PI-RADS 5. Thus, the prevalence of PI-RADS 4/5 and PI-RADS 3 PSAD > 0.15 is estimated at 60%. The estimated prevalence of csPCa in this cohort is 50%, and the detection of low-grade PCa (ISUP 1) is expected to be 15%.

Based on prior evidence, targeted biopsy alone is expected to reduce ISUP 1 detection by at least 40% [7], and SB adds approximately 5% absolute incremental csPCa detection according to randomized trials and a Cochrane meta-analysis [9, 10, 13, 14]. Non-inferiority of TB alone compared with TB + SB will be evaluated by testing H0: Δ0 = πTB − πSB + TB ≤ − δNI, with a non-inferiority margin of δNI = 13%. The non-inferiority margin of 13% was chosen based on prior evidence demonstrating an approximate 4–5% incremental detection of clinically significant prostate cancer with systematic biopsy, allowing for a conservative margin that maintains clinical relevance. Assuming πSB + TB = 50% and a true difference of Δ = − 5%, 477 patients per arm ensure 80% power at one-sided α = 0.05.

Superiority in avoiding ISUP 1 diagnoses will be tested under H0: πTB/πSB + TB ≥ 1. With πSB + TB = 15% and a true reduction ratio to 60%, a sample size of 460 patients per arm ensures 88% power at *α* = 0.05.

Therefore, 1590 analyzable patients are required (2 × 477/0.6 = 1590), and accounting for 20% dropout, approximately 1908 must be allocated within 3 years.

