**Discussion:**

PRIMA will provide high-level evidence whether systematic biopsy can be safely omitted in MRI-positive biopsy-naïve men, potentially reducing diagnostic morbidity and overtreatment.

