## Introduction

### Background and rationale {6a}

In the German healthcare context, optimizing diagnostic efficiency is essential due to increasing demand for prostate cancer screening and limited reimbursement for mpMRI. Although MRI-targeted pathways have demonstrated clinical effectiveness, evidence for their cost-effectiveness and scalability in Germany remains limited. PRIMA addresses this gap by evaluating a high-quality, quality-assured MRI pathway that could reduce unnecessary biopsies and downstream treatment costs while maintaining diagnostic accuracy. Prostate cancer (PCa) is the most common solid cancer among men in Germany, with around 75,000 new diagnoses and 15,000 deaths annually, representing 25% of new male malignancies [1]. Classical diagnostic algorithms combining PSA, DRE, and 12-core SB lead to both overdetection of indolent PCa and missed csPCa [2]. Overdiagnosis results in unnecessary treatment, side effects, and psychological burden, whereas underdetection may delay curative therapy. Several prospective studies have demonstrated that TB alone provides similar detection proportions of csPCa compared with SB, while significantly lowering detection of clinically insignificant cancers [3–7]. Nonetheless, other reports suggest that SB still adds incremental diagnostic value [8–13]. The absolute additional yield of SB for csPCa detection has been estimated at 4–5% in two randomized trials and a Cochrane review [8–10], while TB alone may reduce the detection of ISUP grade group 1 cancers by up to 40% [7]. More recent data from the PROBASE trial in younger men (45–55 years) in a screening setting demonstrated that SB identified 26% additional csPCa compared with TB alone, whereas TB contributed only 6% additional csPCa [14]. Screening trials such as STHLM3-MRI [11] and Göteborg-2 [12] provided population-level insights. In STHLM3-MRI, MRI-based pathways reduced unnecessary biopsies and detection of low-grade cancers but would have missed ~1.7 csPCa cases for each avoided ISUP 1 diagnosis [11]. Göteborg-2 demonstrated comparable csPCa detection between TB-only and combined strategies, with fewer insignificant cancers in the TB-only arm (0.6% vs 1.2%), though some intermediate-risk cancers were detected only by SB [12]. Together, these studies highlight that MRI-targeted pathways can safely reduce overtreatment but may risk missing a small proportion of csPCa. Within Germany, mpMRI before biopsy is guideline-recommended [15]. However, the routine addition of SB remains under debate. The PROBASE trial, focusing on younger men (45–55 years), revealed that SB detected 26% additional csPCa compared to TB, suggesting that MRI interpretation and tumor biology may differ with age [16]. Furthermore, the PRIME trial recently demonstrated that bpMRI could suffice in older men (median age 65) [17], whereas PRIMA intentionally uses mpMRI to address potential diagnostic challenges in younger and intermediate-risk groups [18, 19]. Beyond diagnostic accuracy, PRIMA integrates patient-reported outcomes (PROs) to assess procedural burden (VAS) and quality of life (EORTC-QLQ-C30, EPIC-26). These outcomes are essential as biopsy techniques evolve from transrectal to transperineal approaches, potentially reducing infection risk and improving patient experience [13]. Quality assurance (QA) is a major element of PRIMA: all radiology centers are Q2-certified, ensuring compliance with PI-RADS v2.1 [20] and PI-QUAL v2 [21] standards, while urologists must document proficiency in ≥ 100 fusion biopsies. Despite robust international data, most trials have mixed cohorts with prior biopsy history, different MRI protocols, or lacked uniform QA. PRIMA is unique in enrolling exclusively biopsy-naïve men with well-defined MRI risk thresholds (PI-RADS 4/5 or PI-RADS 3 with PSAD > 0.15) and applying a standardized national QA framework. The study therefore aims to generate definitive evidence for or against omission of SB in MRI-positive men within a German healthcare setting.

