## Interventions

### Explanation for the choice of comparators {6b}

The comparator arm (TB + SB) reflects the current standard of care recommended in national and international guidelines and widely practiced across Germany and Europe. Systematic biopsy remains routine in biopsy-naïve men because prior evidence suggests a potential incremental diagnostic yield of approximately 4–5% for clinically significant prostate cancer (csPCa) when added to targeted biopsy. Therefore, TB + SB serves as the appropriate control against which the non-inferiority of TB-only can be rigorously evaluated.

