#### Secondary outcomes

Patient-reported outcomes (EPIC-26, EORTC-QLQ-C30, VAS)

Measured using validated questionnaires (metric: continuous scores), analyzed as mean changes over time and between groups (aggregation: mean differences), assessed at baseline, 30 days, and 12 months.Biopsy-related complications

Defined as adverse events within 30 days post-biopsy (measure: clinical assessment; metric: categorical/binary), summarized as proportions by study arm, assessed at 30 days post-procedure.Biopsy avoidance due to mpMRI triage

Defined as the proportion of participants not undergoing biopsy due to non-suspicious mpMRI findings (PI-RADS 1–2 or PI-RADS 3 with PSAD ≤ 0.15), reported as proportion, assessed at screening.Diagnostic performance of DRE

Defined as the association between DRE findings and biopsy outcomes (metric: sensitivity, specificity), analyzed cross-sectionally at baseline and biopsy.Biopsy approach (transrectal vs. transperineal)

Compared in terms of pain (VAS score) and infection rates (binary), summarized as mean differences and proportions, assessed within 30 days post-biopsy.MR in-bore biopsy yield

Defined as detection of csPCa in participants undergoing MR in-bore biopsy after negative or ISUP 1 results (metric: binary), reported as proportion, assessed within 3 months post-biopsy.Detection of higher-grade cancer (ISUP ≥ 3)

Defined as presence of ISUP ≥ 3 cancer on histopathology (metric: binary), reported as proportion, assessed at index biopsy.Comparison of bpMRI vs mpMRI

Retrospective comparison of detection performance (metric: paired binary outcomes), analyzed using constrained maximum likelihood methods, assessed at baseline imaging.Change in PI-RADS score

Defined as change in PI-RADS category between baseline and follow-up MRI (metric: ordinal change), reported as proportions of up- or downgrading, assessed at 12 months.Index-lesion-only analysis

Detection of csPCa based on index lesion targeting only (metric: binary), reported as proportion, assessed at index biopsy.AI and radiomics validation

Diagnostic performance of AI-based models (metric: AUC, sensitivity, specificity), analyzed retrospectively, assessed using baseline imaging and biopsy outcomes.

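### The 13-point margin is called conservative but is 2.6 to 3.25 times the 4–5 point yield that justifies it, so the non-inferiority verdict alone cannot support omitting systematic biopsy

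*Protocol article*

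**What the plan says.** The Sample size section sets the margin and gives its basis in one sentence: "The non-inferiority margin of 13% was chosen based on prior evidence demonstrating an approximate 4–5% incremental detection", "allowing for a conservative margin that maintains clinical relevance". The same section states that "SB adds approximately 5% absolute incremental csPCa detection" and plans on 50% csPCa in Arm B, a true difference of −5 points, one-sided α of 0.05, 80% power and 477 men per arm. The 4–5 point figure recurs in the Background ("The absolute additional yield of SB for csPCa detection has been estimated at 4–5% in two randomized trials and a Cochrane review") and in the rationale for the comparator ("potential incremental diagnostic yield of approximately 4–5% for clinically significant prostate cancer").

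The statistical methods section names the Gart and Nam score test on the absolute difference, at one-sided 0.05. The abstract promises "high-level evidence whether systematic biopsy can be safely omitted". The main Discussion links guideline updates, reimbursement and possible nationwide implementation to the trial, the last of these if non-inferiority is shown.

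**The concern.** SB is the only planned difference between the arms, so its added yield is what Arm A gives up. A margin derived from that yield would normally lie below it, so that passing the test shows some of the yield is kept. Here the margin is well above it, and no step from 4–5 to 13 is given. The planning scenario is itself a loss of all that SB is assumed to add, and the trial is sized to pass in that case.

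What is at stake is the meaning of the primary result. A reader who is told that the margin was conservative will take a pass as evidence that little or nothing is lost without SB, when a pass is the expected outcome if the full assumed yield is lost.

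**Working it through.** **Inputs**, all from the Sample size and statistical methods sections: margin 0.13, Arm B 0.50, Arm A 0.45, one-sided α 0.05, 477 per arm, score test on the difference.

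**1. The plan's own figure.** With the variance restricted under the null, the proportions are 0.4105 and 0.5405, so V0 = 0.4105 × 0.5895 + 0.5405 × 0.4595 = 0.4904. Under the alternative, V1 = 0.45 × 0.55 + 0.50 × 0.50 = 0.4975.

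n = (1.645 × √0.4904 + 0.842 × √0.4975)² / (0.13 − 0.05)² = 476.02, so 477 per arm. The stated number reproduces, and the arithmetic is not in dispute.

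**2. Margin against its basis.** 13 / 5 = 2.6 and 13 / 4 = 3.25. Against the control rate, 13 / 50 = 26%.

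**3. Worst observed result that still passes.** With Arm B at 50%, the score statistic meets 1.645 when Arm A is at 42.3%. That is a loss of about 7.7 points, or 7.7 / 50 = 15% of the csPCa detected in Arm B. At −7.7 points the score intervals are:
- 90%: −13.0 to −2.4
- 95%: −14.0 to −1.4

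Both exclude zero, so TB would be declared non-inferior and be significantly worse in the same analysis.

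**4. Chance of declaring non-inferiority by true loss L.** Power = Φ{[(0.13 − L) × √477 − 1.645 × √V0] / √V1}, with V0 and V1 recalculated at each L:

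| True loss (points) | Chance of passing |
|---|---|
| 4 | 88% |
| 5 | 80% |
| 6 | 70% |
| 8 | 47% |
| 10 | 24% |
| 13 | 5% |

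Losing the whole 4–5 point yield therefore passes 80% to 88% of the time.

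**5. What the interval can still do.** If the observed difference is near 0, the lower 90% limit is about −1.645 × √(0.50 / 477) = −5.3 points. The estimate can be informative where the verdict is not.

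**6. Within-arm information.** Arm B men receive both procedures. If 24 of 477 (5%) had csPCa in SB cores only, the exact 95% interval would be 3.2% to 7.4%. The between-arm 95% half-width is 1.96 × √(0.4975 / 477) = 6.3 points. These are different quantities, so the comparison shows only that the SB-only yield can be estimated closely with the planned men. It assumes that TB and SB cores are reported separately, which the article does not state.

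**The case against.** Several stronger readings are tempting, and the documents do not support them.

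- **That 13 points exceeds every SB benefit the article cites.** The Background also reports that "SB identified 26% additional csPCa compared with TB alone", from a screening trial in men aged 45–55, without saying whether this is relative or absolute. If it is relative (an assumption), at a 50% rate it is 50 − 50/1.26 = 10.3 points, or 0.26 × 50 = 13 points. The margin would still equal or exceed it. Only an absolute 26 points would exceed the margin, and that conflicts with the planning value of 5. The ratio of 2.6 to 3.25 is thus stated only for the 4–5 points in the margin's rationale.
- **That the trial cannot answer its question.** This is true of the pass/fail verdict only; the interval may exclude smaller losses. The trial also weighs csPCa against a co-primary reduction in ISUP 1, so some csPCa loss could be judged acceptable. That judgement would need to be argued, and the margin's rationale does not mention it.
- **That the Arm B paired data will not be analysed.** No within-Arm-B comparison is among the listed outcomes and analyses; the nearest is "Detection of csPCa based on index lesion targeting only". But the SAP and full protocol are not shown, so the omission cannot be confirmed.
- **That the paired estimate would settle the matter.** It would not. Operators know that SB will follow, SB cores may hit the lesion, and a within-arm increment cannot be negative, unlike the randomised difference.
- **That 15% of cancers would be missed for good.** The figure refers to index biopsy. In-bore biopsy and follow-up MRI may find some later, though neither alters the endpoint or the margin.

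These points narrow the claim. None of them makes 13 conservative relative to 4–5.

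**Conclusion.** The point stands in limited form. The stated property of the margin is wrong: it is 2.6 to 3.25 times the yield it is derived from and preserves none of it. At 477 per arm and 50% in Arm B, a pass is compatible with an observed loss of about 7.7 points and has an 80% chance at the full assumed loss of 5. The verdict alone cannot carry the abstract's claim about safe omission or the Discussion's claim about implementation. The sample size calculation is correct for the margin chosen.

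The figures assume a 50% Arm B rate, 477 analysed men per arm and a normal approximation for the score test.

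**What to change.** 1. Delete the word conservative. State that the margin is about 2.6 to 3.25 times the 4–5 point yield used to justify it, and note that the 26% figure comes from a younger screening population on an unstated scale.
2. Limit the non-inferiority conclusion to this: a loss of 13 points or more is excluded at one-sided 0.05. Report the two-sided 90% score interval, which matches the test, with the 95% interval alongside, and read both explicitly against a 4–5 point loss. The 90% interval is needed because, for observed losses of about 6.7 to 7.7 points, the test passes while the 95% interval includes −13. Align the abstract and Discussion with this conclusion.
3. Pre-specify, as a supportive secondary analysis, the proportions of Arm B men with csPCa found only in SB cores and only in TB cores, with exact 95% intervals. Record TB and SB histology separately in the eCRF. If the SAP already contains this, refer to it.

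The cost is protocol and SAP wording, one eCRF distinction and a narrower claim. No extra patients are needed. Tightening the margin would be far dearer: with a true loss of 5 points and the unpooled formula, a 10-point margin needs (1.645 + 0.842)² × 0.4975 / 0.05² ≈ 1,231 per arm, and a margin of 5 or less cannot be powered at all. The article reports no enrolment at manuscript submission, with recruitment planned from 15 April 2026, so the eCRF change is cheapest if made early.

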**Sample size:**

One thousand nine hundred eight men were allocated to achieve 1590 analyzable patients (> 80% power; non-inferiority margin δ = 13%).

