### Study setting {9}

The University Hospital Düsseldorf and the German Cancer Research Center (DKFZ) coordinate the trial.

Eight study sites in North Rhine-Westphalia, Germany: five university hospitals (Aachen, Cologne, Düsseldorf, Essen, Herne) and three community hospitals (Mönchengladbach, Essen-Mitte, Recklinghausen).

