#### Feasibility

More than 2500 fusion biopsies are performed annually across participating centers. Recruitment expectations: 1908 within 36 months (636/year; ~64 per center/year; 51 analyzable). PRIMA recruitment does not depend solely on community referrals but is expected to be supported due to advantages for patients such as cost-covered mpMRI and biopsy avoidance in negative imaging cases.

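### The enrolment target of 1908 tolerates a 16.7% loss rather than the stated 20%, and the per-centre rate of about 64 a year does not fit eight centres

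*Protocol article*

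**What the plan says.** The Sample size section sets 477 men per arm for the csPCa non-inferiority test (80% power, one-sided 0.05) and quotes 460 per arm for ISUP 1 (88% power). It divides by the 60% of men expected to be randomized: "Therefore, 1590 analyzable patients are required". It then states "accounting for 20% dropout, approximately 1908 must be allocated within 3 years". Under Assessment for eligibility the target appears as "1908 (including 20% calculated loss", next to an analysis requirement of "477 patients per randomized arm A/B".

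Feasibility spreads the target over time and sites: "1908 within 36 months (636/year; ~64 per center/year; 51 analyzable". Study setting names the sites: "Eight study sites in North Rhine-Westphalia, Germany". The Methods part of the Abstract and the Recruitment section also give eight.

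The Abstract says that 1908 "men were allocated to achieve 1590 analyzable patients" and attaches the power and the margin to that figure.

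**The concern.** Two figures looked inconsistent with their own inputs. First, a loss expressed as a share of those enrolled is allowed for by dividing by one minus that share. Here the analysable number was multiplied by one plus the share, which gives a smaller target. The 477 per arm reaches 80% power with almost nothing to spare, so any shortfall takes the power below the stated value. Second, the per-centre rate does not multiply back to the annual total over the sites named. A site plan built on it would fall short of the target.

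At stake are the accuracy of the stated power under the plan's own loss assumption, and a site-level recruitment figure that investigators may work to. The Abstract adds a smaller problem of wording: its power statement sits on a number that includes men who are never randomized.

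**Working it through.** **Inputs, all from the Sample size section and its sub-sections unless noted.** 477 per arm; share randomized 0.60; loss 20%; target 1908; csPCa 50% with TB + SB and 45% with TB; margin 13 points; one-sided α 0.05; ISUP 1 15% and 9%; 460 per arm for ISUP 1; 636 per year; about 64 per centre per year, 51 analysable; eight centres (Study setting, Recruitment).

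**1. Reproduce the plan's figures.**
- Analysable men: 2 × 477/0.6 = 1590. Matches.
- Score-type non-inferiority calculation (variance under the null from restricted maximum likelihood): 477 per arm for 80% power. Matches exactly. The unpooled normal approximation gives 481.
- ISUP 1, 460 per arm, one-sided 0.05: power 87.7%. Matches the stated 88%.
- Target: 1590 × 1.2 = 1908. Matches exactly, but only in this multiplicative form.

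**2. What 1908 tolerates.**
- Implied loss: 1 − 1590/1908 = 16.7%.
- Target for a 20% loss: 1590/(1 − 0.20) = 1987.5, so 1988, which is 80 more than 1908.
- Check: 1988 × 0.8 × 0.6/2 = 477 per arm.

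**3. Which meaning of 20% the plan uses.** Feasibility turns 64 into 51, and 64 × 0.8 = 51.2. An add-on rule would give 64/1.2 = 53. So Feasibility takes 20% off those enrolled, while the Sample size paragraph adds 20% to those analysed.

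**4. Consequence under the plan's own loss rule.**
- Analysable: 1908 × 0.8 = 1526.
- Per arm: 1908 × 0.8 × 0.6/2 = 458, which is 19 below 477 and 2 below 460.
- Unpooled power is Φ[(0.13 − 0.05)/√(0.4975/n) − 1.645], where 0.4975 = 0.50 × 0.50 + 0.45 × 0.55.

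| n per arm | NI power, unpooled | NI power, score | ISUP 1 power |
|---|---|---|---|
| 477 | 79.7% | 80.1% | 88.7% |
| 460 | 78.5% | 78.8% | 87.7% |
| 458 | 78.3% | 78.7% | 87.6% |

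**5. Dependence on when the loss occurs.** With 1908 enrolled, 1908 × 0.6/2 = 572.4 men per arm before any loss. If a share L is lost before the index biopsy, 572.4 × (1 − L) remain: 458 at L = 20%, 477 at L = 16.7%, 515 at L = 10%.

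**6. Per-centre rate.**
- Eight centres: 636/8 = 79.5 enrolled per year, and 79.5 × 0.8 = 63.6 analysable.
- Printed figures: 64 enrolled and 51 analysable. These equal 636/10 = 63.6 and 63.6 × 0.8 = 50.9.
- Eight centres at 64 for three years: 64 × 8 × 3 = 1536, which is 372 below 1908.
- For a target of 1988: 1988/3/8 = 82.8 per centre per year.

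**7. Abstract.** Randomized men who carry the power: 2 × 477 = 954, not 1590.

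**The case against.** The strongest defence is that the first slip is small and may not materialize. Both co-primary outcomes are assessed at the index biopsy, while follow-up runs to 12 months and the retention measures are aimed chiefly at the 30-day and 12-month visits. The document does not say when the 20% is lost. Loss after biopsy removes nobody from the primary endpoint, and the primary analysis includes all randomized men with multiple imputation. This stands as a limit on size: 477 is reached once pre-biopsy loss is 16.7% or less. It does not rescue the figure, because the plan itself charges the whole 20% against the analysable set. Nor can the 20% be read as a simple add-on: "including 20% calculated loss" describes a part of the 1908, and Feasibility uses it that way.

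On the per-centre rate, a reader might infer that the trial will finish with about 369 per arm (1536 × 0.8 × 0.6/2) and about 70–71% non-inferiority power. The document does not support that. The rate is given as an expectation, not as a cap or quota, and the same sentence keeps 1908 and 636 per year. The 369 arises only if every site stops at 64 and the full loss also falls before biopsy.

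A reader might also infer that the plan was built for ten centres. That is not established: 64 also equals the eight-centre rate after a 20% loss (79.5 × 0.8 = 63.6), in which case 51 takes the loss off twice. The printed pair is wrong for eight centres on either account.

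On the Abstract, the Sample size section already makes clear that the power belongs to 477 per arm, and the non-randomized men do contribute to the biopsy-avoidance outcome. That part is a matter of wording only.

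**Conclusion.** Both figures are wrong as written, and the consequence is modest. The target of 1908 tolerates a 16.7% loss. Under the plan's own rule that 20% of those enrolled are not analysable, it yields about 458 per arm and non-inferiority power of about 78.3–78.7%, roughly 1.4 points below what 477 gives. ISUP 1 power is essentially unchanged; falling 2 below the quoted 460 has no practical effect. This rests on the plan's rates, on 60% being randomized, on loss being unrelated to MRI category, and on the whole loss falling before the index biopsy. If part of it falls later, the shortfall shrinks or disappears, so it would go too far to say that 477 per arm cannot be reached.

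The per-centre rate should be 79.5, not 64. This changes neither the total nor the annual figure; it matters only if sites plan to it. The 477 and 460 per-arm figures reproduce and are not in question.

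**What to change.** 1. In Sample size and Assessment for eligibility, choose one of three statements: 1908 tolerates a 16.7% loss; or a 20% loss leaves about 458 per arm with about 78.5% non-inferiority power; or the target is 1988, which holds 477 per arm at a 20% loss.
2. In Feasibility, give about 80 enrolled and about 64 analysable per centre per year if 1908 is kept, or about 83 enrolled if 1988 is used.
3. In the Abstract, attach the power and margin to the 954 randomized men (477 per arm), with 1590 as the number of analysable men from whom they come.

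The first two options under item 1 cost only corrected text, with a slightly less favourable loss or power figure. The third adds 80 men, about 3 more per centre per year. Trial status reports that nobody had been enrolled when the article was submitted, so at that point any of these could be made without touching accrued data.
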